#### Adverse events

Participants will be instructed to inform members of the study team of any adverse events they experience while enrolled in the study. Mild and moderate adverse events will be regularly reported to the University of Colorado Boulder Institutional Review Board (IRB), National Institutes of Health, and the study data safety monitoring board. Serious adverse events will be reported to the study medical director within 24 h of the study team’s awareness of the adverse event and to the University of Colorado Boulder IRB within 5 days. An unanticipated adverse event which meets the University of Colorado Boulder IRB definition of an unanticipated problem (i.e., any unanticipated and undesirable effect arising from participation in research that results in an increased risk of harm or injury to a subject, or which suggests the possibility of increased risks to other subjects) will be reported to the University of Colorado Boulder IRB using the corresponding form within 5 days of occurrence.

#### Statistical design, power, and analysis plan

Sample size calculations and pre-determined statistical power for this randomized, single-blind, parallel group design clinical trial are based on the results from the estrogen-deficient postmenopausal women enrolled in our IMST pilot study (Craighead et al., 2021b) and results from a meta-analysis on the effects of aerobic exercise on SBP in our target population (Kelley, 1999).

Accordingly, it was estimated that aerobic exercise reduces casual SBP by 3.0 ± 3.7 mmHg (mean ± standard deviation), while high-resistance IMST reduces casual SBP by 7.6 ± 7.4 mmHg. With these parameters, it was estimated that 36 subjects per group (72 total) would provide 90% power to detect a difference in the change in casual SBP between groups with a two-sided type I error rate of *p* = 0.05. To account for a potential dropout rate of ∼20%, we will enroll 45 participants into each group (90 participants total).

Block randomization by age (midlife: ≤64 years; older ≥65 years) and baseline SBP (elevated SBP/stage 1 hypertension: 120–139 mmHg; stage 2 hypertension: ≥140 mmHg) will be employed. Data for all outcome variables will be collected at baseline and at the end of the respective 3-month interventions. In addition, casual BP, 24-h BP and FMD_BA_ will be collected after abstaining from the interventions for 6 weeks to assess potential persistent effects of previous training on these outcomes.

Descriptive statistics will be calculated for all baseline and outcome variables. Means and standard deviations will be calculated for all continuous variables, and frequency and proportion will be provided for all categorical variables. Data transformation will be performed if appropriate. The 95% confidence interval will be calculated as needed.

Repeated measures analysis by linear mixed effects models will be used to assess changes in casual and 24-h BP and FMD_BA_. Data from baseline, end-intervention and 6 weeks after completing the intervention will be included in the model. Based on this model, comparisons in the changes in BP between the two groups will be performed to assess the treatment effect. The basic model will include group, measurement timepoint, and the group by time interaction. Potential confounders such as time post menopause or use of antihypertensive medications can be included for adjustment purposes.

The same linear mixed effects model will be used to evaluate the intervention effect on our mechanistic outcomes at baseline and end-intervention. In addition, the association between the change in FMD_BA_ and changes in mechanistic probes will be assessed and linear regression model analysis used to adjust for potential confounders. Finally, mediation analysis will be used to provide evidence for a potential causal influence of our mechanistic probes for contributing to changes in FMD_BA_ with IMST or aerobic exercise (Mascha et al., 2013; Valente et al., 2017).

Adherence will be calculated as the percentage of prescribed training sessions performed appropriately and compared between groups with an unpaired t-test. Safety and tolerability will be described qualitatively.

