### Other outcomes

#### Oxidative stress-associated suppression of endothelial function

Tonic suppression of endothelial function by oxidative stress will be assessed by measuring the improvement in FMD_BA_ from baseline (saline control) in response to acute (intravenous) infusion of supraphysiological concentrations of vitamin C, a potent antioxidant that scavenges reactive oxygen species (ROS) (Eskurza et al., 2004; Walker et al., 2012; Jablonski et al., 2013). A bolus dose of 0.06 g vitamin C/kg fat-free mass dissolved in 100 ml of saline will be infused intravenously at a rate of 5 ml/min for 20 min, followed immediately by a “drip-infusion” of 0.02 g/kg fat-free mass dissolved in 30 ml of saline infused at a rate of 0.5 ml/min. FMD_BA_ will be performed as described above at the end of the 20-min bolus during the “drip infusion,” when peak levels of vitamin C occur (Eskurza et al., 2004).

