**FIGURE 3 F3:**
[figure not shown]
Expected Results. Expected results for **(A)** casual systolic blood pressure (SBP; primary outcome) and 24-h SBP (secondary outcome); and for **(B)** endothelial function measured by brachial artery flow-mediated dilation (FMD_BA_; secondary outcome) in the high-resistance inspiratory muscle strength training (IMST) and moderate-intensity aerobic exercise groups across the intervention. Dashed line represents expected FMD_BA_ with supratherapeutic infusion of the potent antioxidant, vitamin C, in both subject groups.

We also expect a greater improvement in FMD_BA_ following high-resistance IMST compared to aerobic exercise training, and that the improvement in FMD_BA_ following IMST will be at least partially sustained 6 weeks later (Figure 3B).

At end-intervention, we anticipate that high-resistance IMST will reduce or abolish the acute increase in FMD_BA_ observed after systemic infusion of vitamin C at baseline, but that aerobic exercise training will have no effect (Figure 3B). We expect that in biopsied endothelial cells, high-resistance IMST will decrease nitrotyrosine (marker of oxidative stress), decrease the expression of the oxidant enzyme NADPH oxidase, and increase expression of the antioxidant enzyme MnSOD to a greater extent than aerobic exercise training. We also expect endothelial cells cultured with subject serum obtained after (vs. before) IMST will increase NO and decrease ROS production more than serum obtained after (vs. before) aerobic exercise training. We also expect to identify changes in circulating metabolites with IMST that more greatly modulate endothelial cell NO and ROS production than aerobic exercise training does.

In addition, we expect to observe higher rates of adherence to the high-resistance IMST intervention compared to aerobic exercise training. Finally, we expect to observe fewer intervention-related adverse events and dropouts due to adverse events in the IMST group, suggesting greater safety and tolerability of IMST compared to aerobic exercise.

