Finally, this current trial features additional outcome measures not assessed in any previous trial on high-resistance IMST. These outcomes include *in vivo* assessment of reactive oxygen species-associated suppression of vascular endothelial function, biopsied endothelial cell protein markers of oxidative stress, vascular smooth muscle sensitivity to NO, and *ex vivo* endothelial cell production of NO and ROS following administration of serum or other experimental manipulations to provide insight into mechanisms of action. In addition, along with casual SBP, the persistent effects of IMST and aerobic exercise on 24-h SBP and vascular endothelial function following the cessation of the respective interventions will be measured. Overall, there are a significant number of novel and innovative aspects of this trial that will provide important new information regarding high-resistance IMST as a potential healthy lifestyle intervention.

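### The vitamin C probe contains resting FMD with a minus sign, so its change should not be associated with the change in FMD or used as a mediator of it

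*Protocol article*

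**What the plan says.** Under Oxidative stress-associated suppression of endothelial function, the probe is "assessed by measuring the improvement in FMD_BA_ from baseline (saline control) in response to acute (intravenous) infusion" of vitamin C. The vitamin C reading is the same kind of scan as the secondary outcome: "FMD_BA_ will be performed as described above at the end of the 20-min bolus". The probe is therefore FMD on vitamin C minus FMD on saline.

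Novelty and innovation lists "assessment of reactive oxygen species-associated suppression of vascular endothelial function" among the measures meant to show how the intervention works, so it is most naturally one of the mechanistic probes.

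Statistical design, power, and analysis plan fits a mixed model to the mechanistic outcomes at baseline and end-intervention. It then adds two analyses. In the first, "the association between the change in FMD_BA_ and changes in mechanistic probes will be assessed", with "linear regression model analysis used to adjust for potential confounders". In the second, "mediation analysis will be used to provide evidence for a potential causal influence of our mechanistic probes for contributing to changes in FMD_BA". No probe is excluded from either, and nothing is said about a term shared between probe and outcome.

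Expected results and their interpretation predicts that "high-resistance IMST will reduce or abolish the acute increase in FMD_BA_ observed after systemic infusion of vitamin C at baseline", alongside a rise in FMD.

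**The concern.** A rise in saline FMD, real or due to reading error, lowers the vitamin C increment one for one unless vitamin C FMD rises with it. Relating the change in that increment to the change in FMD can therefore give a negative association because the same quantity enters both with opposite signs. Adjusting for confounders does not help, because the shared term is part of the probe's definition and not a third variable.

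The artefact has the same shape as the predicted result: FMD up, vitamin C response down. A causal statement about oxidative stress could then rest partly on arithmetic.

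**Working it through.** **The plan's own figure.** The only design calculation is for casual systolic pressure. With a difference of 7.6 − 3.0 = 4.6 mmHg and SD √((3.7² + 7.4²)/2) = 5.85, power at 36 per group is 0.916 (normal), 0.908 (pooled t) or 0.905 (Welch). Enrolment is 36/(1 − 0.2) = 45 per group. The stated 90% power, 72 completers and 90 enrolled are reproduced. There is no calculation for the probe analyses, and the article gives no FMD variances or correlations, so those below are assumptions shown over a range.

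**Association, saline scan = outcome scan.** Let ΔS and ΔV be the changes in saline and vitamin C FMD, with equal SD σ and correlation ρ. The probe change is ΔV − ΔS.

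- Cov(ΔS, ΔV − ΔS) = ρσ² − σ² = −(1 − ρ)σ²
- Var(ΔV − ΔS) = 2(1 − ρ)σ²
- Corr = −(1 − ρ)/√(2(1 − ρ)) = −√((1 − ρ)/2)

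| ρ | built-in r | significant at two-sided 0.05, n = 72 |
|---|---|---|
| 0 | −0.71 | about 100% |
| 0.5 | −0.50 | 99.6% |
| 0.75 | −0.35 | 87% |
| 0.9 | −0.22 | about 47% |

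The first three rates come from 4,000 simulated trials. The last is the Fisher z approximation: atanh(0.2236) × √69 = 1.89, and Φ(1.89 − 1.96) = 0.47.

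With unequal SDs, k = SD(ΔV)/SD(ΔS), the correlation is (ρk − 1)/√(1 + k² − 2ρk). Over k = 0.5 to 1.5 and ρ = 0 to 0.9 it runs from −0.93 to +0.47. It is mostly negative, and turns positive only when k exceeds 1 and ρ is high.

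**Same scan or separate scan.** Further simulation used 3,000 trials per setting, 36 women per group, SD of true FMD change 1, measurement-error SD of a change 0.5, 1 or 1.5, and a group effect on FMD of 0 or 1. Vitamin C FMD moved exactly in step with saline FMD, so the true probe change was zero.

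- Shared scan: mean r −0.29 to −0.59, significant in 69% to 100% of trials.
- Separate outcome scan: mean r 0.00, significant in 4.5% to 5.6%.

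The formula agrees. Here ρ = 1/(1 + error variance) = 0.80, 0.50 and 0.31, which gives −0.32, −0.50 and −0.59; the simulated values with no group effect were −0.31, −0.50 and −0.59.

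**Mediation.** An indirect effect needs both a group difference in the probe and a probe–outcome association given group. It was called significant when both were.

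- True probe change zero, shared scan: significant in about 4% to 5% of trials, mean indirect effect about 0, even with a real group effect on FMD.
- Vitamin C FMD flat, group effect 1 on saline FMD:

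| error SD | shared: significant | shared: share mediated | separate: significant | separate: share mediated |
|---|---|---|---|---|
| 0.5 | 93% | 83% | 93% | 67% |
| 1 | 66% | 66% | 65% | 33% |
| 1.5 | 43% | 59% | 20% | 18% |

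The share mediated is the mean indirect effect over the mean total effect, for example 0.664/1.001 = 66%. In this setting the probe change is the FMD change with its sign reversed, plus noise, so a separate scan reduces the dependence without removing it.

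**The case against.** A reader might infer that the oxidative-stress aim would be confirmed whatever the truth. The documents do not support that, for three reasons.

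- **Mediation is not automatic.** It also needs a group effect on the probe. When vitamin C FMD rises in step with saline FMD, the test keeps roughly its nominal error rate. The flat pattern that inflates it is also what the oxidative-stress hypothesis predicts. What remains is a rival explanation, a non-oxidative gain in FMD under a ceiling, which the analysis cannot tell apart from the hypothesis.
- **The aim does not rest on these analyses.** The group-by-time mixed model on mechanistic outcomes comes first; association and mediation are additions, worded as evidence of a potential influence. Nitrotyrosine, p47phox, MnSOD and the serum-exposed HUVEC measures share no term with FMD.
- **The outcome scan is not identified.** Vascular endothelial function describes FMD without an infusion, and baseline and end-intervention testing each span three visits. Treating the saline scan as the outcome is natural but not stated.

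Two further objections carry weight. The magnitudes rest on assumed SDs and correlations. If vitamin C truly adds nothing, ρ should be high unless reading error dominates, which favours the smaller figures. A condensed article may also leave the list of mediators to a fuller document. But the article itself commits to both analyses across the probes and gives the causal reading, so this is more than missing detail.

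**Conclusion.** The concern holds for the vitamin C probe only. With a shared saline scan, the planned association is generally biased negative with no oxidative mechanism: r from about −0.71 to −0.22 under equal SDs as ρ goes from 0 to 0.9, with wider values and a possible sign reversal otherwise. With a separate outcome scan and no true probe change there is no artefact. Mediation is at risk when vitamin C FMD stays flat, a pattern compatible with the predicted result. Under the assumed variances, 59% to 83% of the FMD effect then appears mediated with a shared scan and 18% to 67% with a separate one, partly by arithmetic. The change is worth making, but it concerns supporting analyses: the primary blood pressure analysis, the group comparison of FMD and the sample size stand.

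**What to change.** Exclude the vitamin C difference score from the association and mediation analyses of FMD. Test it only through the group-by-time model already planned for mechanistic outcomes. Since the score is vitamin C minus saline FMD, this is the same contrast as group × time × infusion in a joint model of the two readings, so no test of the hypothesis is lost.

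Keep association and mediation for the probes measured independently of FMD: nitrotyrosine, p47phox, MnSOD and serum-exposed HUVEC NO and ROS.

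State which scan supplies the outcome FMD. If the difference score is kept as a sensitivity analysis, use an outcome scan separate from the saline control and state the structural dependence that remains.

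The cost is a few sentences in the analysis plan and no new data. One probe leaves the mediation set.

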#### Safety and tolerability

Safety, i.e., risk to the subject, of both treatment arms will be assessed by recording adverse events during the intervention. Tolerability, i.e., the degree to which overt adverse events are tolerated by participants, will be determined based on the number of participants that drop out of the study due to adverse events.

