### Novelty and innovation

This study builds on promising findings from our pilot clinical trial that suggested high-resistance IMST may be able to lower SBP and improve endothelial function in a small subset (*n* = 7) of estrogen-deficient postmenopausal women. The larger sample size employed in this properly powered clinical trial will enable us to definitively determine the efficacy of high-resistance IMST in this important population.

The intervention duration for the current protocol was chosen based on clinical guidelines for lifestyle-based treatment of high BP, which recommend 3 months of healthy lifestyle practices as a first-line intervention for lowering BP (Whelton et al., 2018). This intervention duration also will extend the findings from our previous pilot clinical trial, which used only a 6-week IMST intervention (Craighead et al., 2021b). BP continued to decline throughout the intervention period, supporting the possibility that a longer treatment duration would result in further reductions in BP. Overall, our new trial will allow us to examine the magnitude of improvement in cardiovascular function following a longer treatment duration and to assess the safety, tolerability, and adherence profiles of high-resistance IMST over an extended period.

As all previous studies on high-resistance IMST have used a low-resistance sham control group, our new clinical trial will, for the first time, compare IMST to guideline-based aerobic exercise training, thus allowing us to directly assess the relative effectiveness of IMST compared with “standard of care” aerobic exercise. The innovative study design will enable direct comparisons of the safety, tolerability, adherence, efficacy and underlying molecular mechanisms between high-resistance IMST and aerobic exercise.

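### The between-arm safety and tolerability statements do not match the stated qualitative analysis, which names no difference or interval

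*Protocol article*

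**What the plan says.** The section Safety and tolerability (under Other outcomes) makes both concepts countable. Safety "will be assessed by recording adverse events during the intervention" in both arms, and tolerability is judged "based on the number of participants that drop out of the study due to adverse events".

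Two later sections look ahead to a comparison. Novelty and innovation states: "The innovative study design will enable direct comparisons of the safety, tolerability, adherence, efficacy and underlying molecular mechanisms between high-resistance IMST and aerobic exercise". Expected results and their interpretation forecasts fewer intervention-related adverse events and fewer adverse-event dropouts with IMST, "suggesting greater safety and tolerability of IMST compared to aerobic exercise".

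The section Statistical design, power, and analysis plan deals with these outcomes in one sentence: "Safety and tolerability will be described qualitatively". In the sentence just before it, adherence is to be "compared between groups with an unpaired t-test". Earlier, the same section gives a general rule: descriptive statistics for every outcome variable, frequency and proportion for categorical ones, and a 95% confidence interval where needed.

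**The concern.** The endpoint is a count and the anticipated statement is comparative, but the specific analysis sentence is non-quantitative. This is a mismatch within the text, not a detail left to an analysis plan, because the article states the method. Adherence, named in the same list of direct comparisons, gets a between-group method; safety and tolerability do not.

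At stake is how a small imbalance would be read. With few events per arm, one arm will often have fewer by chance. If that is described in words, without a difference and its interval, the reader cannot see how little it establishes. A statement that IMST is safer or better tolerated than guideline-based walking could then rest on a handful of events.

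**Working it through.** **Inputs from the article.** 36 completers per group, about 20% dropout, 45 enrolled per group (Statistical design, power, and analysis plan). No adverse-event rate is given for either arm. The only related data are from the 6-week pilot of IMST, with no serious adverse events and no dropouts due to adverse events (Background and rationale). All event rates and event patterns below are therefore assumptions.

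**Step 1: the plan's own figure.** 36 / (1 − 0.20) = 45 per group, 90 in total, as stated. The 36 per group also reproduces for casual SBP: difference 7.6 − 3.0 = 4.6 mmHg, root-mean-square SD √((3.7² + 7.4²)/2) = 5.85, two-sided 5%, power 90.8% by the pooled t calculation against the stated 90%. That calculation covers casual SBP only. No figure is stated for safety or tolerability.

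**Step 2: how often IMST shows fewer women with events when nothing differs.** Let X and Y be independent Binomial(45, p). By symmetry P(X < Y) = (1 − P(X = Y)) / 2, with P(X = Y) = Σ P(X = k)².

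| Assumed common true rate p | P(tie) | P(IMST fewer) |
|---|---|---|
| 2% | 0.329 | 34% |
| 5% | 0.198 | 40% |
| 10% | 0.141 | 43% |
| 20% | 0.105 | 45% |

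The forecast direction would thus appear in roughly 34% to 45% of trials with no true difference.

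**Step 3: what zero events establishes.** The two-sided exact 95% upper limit for 0 of n is 1 − 0.025^(1/n). For n = 45 it is 7.9%; for n = 36 it is 9.7%.

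**Step 4: what an interval would show.** Suppose 4 of 45 adverse-event dropouts with walking and 1 of 45 with IMST. The difference is 8.9% − 2.2% = 6.7 points. The Wilson limits are 3.5% to 20.7% and 0.4% to 11.6%. The Newcombe 95% interval is

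- lower: 6.7 − √((8.9 − 3.5)² + (11.6 − 2.2)²) ≈ −4.1 points
- upper: 6.7 + √((20.7 − 8.9)² + (2.2 − 0.4)²) ≈ +18.7 points

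(computed unrounded). With 4 versus 0 the difference is 8.9 points, interval −0.6 to 20.7.

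**Step 5: whether a test would help.** Two-sided Fisher tests with 45 per arm give p = 0.056 for 0 versus 5 and p = 0.026 for 0 versus 6. Exact power at assumed rates (walking versus IMST) is 2% for 5% versus 1%, 15% for 10% versus 2%, and 48% for 20% versus 5%. Adding a test would not let a trial of this size settle the matter.

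**The case against.** Much of the case on the other side stands.

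- A reader might infer that the plan reports nothing numerical on safety. The documents do not support that. Safety and tolerability are listed as outcomes, dropout due to an adverse event is categorical, and the general rule provides frequencies and proportions and, where needed, confidence intervals. The word qualitatively may mean only that no formal test is planned, in contrast to adherence. What remains is that the specific sentence does not say this, and neither sentence names a between-arm difference or its interval.
- A reader might infer that the protocol commits itself to concluding that IMST is safer, or that its analysis could neither support nor contradict that. Both go too far. The statement is a forecast in a section on expected results and is worded as suggesting an advantage. Counts by arm could agree or disagree with it descriptively. The comparative-effectiveness aims in the Introduction cover blood pressure, endothelial function and mechanisms; safety and tolerability are to be assessed further.
- Descriptive safety reporting is normal in a trial this size. Allowing comparative wording only when an interval excludes zero would be an underpowered significance test applied to several endpoints, so it is not proposed.
- Participants cannot be blinded and report their own events. Neither an interval nor counting all events regardless of attribution removes that reporting bias. Counting all events only avoids adding a judgement about relatedness.

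**Conclusion.** The point holds as a mismatch of wording and method. The comparative statements in Expected results and their interpretation and in Novelty and innovation are not matched by the one analysis sentence specific to these outcomes, and that sentence sits uneasily with the general rule in the same section.

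Its size rests on assumed event rates, on 45 randomised women per arm, and on one yes/no outcome per woman. On that basis a chance finding in IMST's favour is common, and an event-free arm does not exclude a true rate approaching 8%. The point is minor: it bears on how safety and tolerability are reported and leaves the primary outcome and its sample size untouched.

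**What to change.** Replace the sentence on qualitative description. State that, by arm and among all randomised women, the number and proportion with (a) any adverse event, (b) any serious adverse event and (c) dropout due to adverse events will be reported, regardless of attribution to the intervention. Give the risk difference and its 95% confidence interval for each, as estimation, with no formal test and no significance threshold. Narrative description of individual events can stay alongside.

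In Expected results and their interpretation and in Novelty and innovation, make the safety and tolerability wording descriptive, and say that any comparative statement will be read against those intervals.

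The cost is a few lines of analysis on data the trial already collects. The downside is that the intervals will be wide and the favourable wording on safety may not be usable.
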